### Inclusion criteria

The only inclusion criterion for teams is that they care for patients with psychotic disorders who have problems adhering to antipsychotic maintenance medication. These are currently dedicated AOTs with a corresponding policy. The only exclusion criteria are lack of willingness to participate and an already existing practice of offering financial incentives to patients with problematic medication adherence.

For patients in the AOTs there are the following inclusion criteria:

• being cared for in the AOT for at least 4 months,

• between 18 and 65 years of age,

• capacity to give informed consent to participate in the study and actual written informed consent,

• an established diagnosis of schizophrenia, schizo-affective psychosis, or bipolar illness according to ICD-10,

• being prescribed depot injections of anti-psychotic medication,

• poor adherence to anti-psychotic medication, i.e. missed 50% or more of prescribed depot injections over the last 4 months (so that the percentage of taken depots is based on a minimum of 4 prescribed depots), and

• failure of all other methods available to the team to ensure adherence to medication.

### Exclusion criteria

Exclusion criteria are:

• learning difficulty

• poor command of English so that clinical communication and discussion of agreements is impaired

### Outcome measures

The primary outcome is adherence to anti-psychotic maintenance medication during the 12 month trial period. Adherence will be measured, objectively, as the percentage of prescribed depot injections actually taken. As the primary outcome, the percentage will be used as a continuous variable. However, we will also analyse the percentage in a dichotomised way, comparing the ratio of patients with 'good' adherence (i.e. =80% of prescribed depots taken [20]) in the two conditions.

Further secondary outcomes are:

a) The time 'slippage' of taking depots, defined as the percentage of the prescribed time interval that has expired before the depot is taken;

b) Clinical improvement as assessed on the Clinical Global Impression Scale (CGI) [21] by the treating consultant psychiatrist at the end of the 12 month period;

b) Number of involuntary and voluntary hospital admissions during the trial period;

c) Costs of care: data on the use and frequency of use of inpatient care, outpatient care (including home visits, home treatment), and other health services during the 12 month treatment period will be obtained from case notes and electronic administrative data bases. Costs for the intervention will be estimated for each participating team from information provided by staff. Established national unit costs will be used to estimate direct health care.

d) The number of attempted and completed suicides, incidences of physical violence, police arrests and days spent at work/training/education will also be recorded over the 12 month trial period.

e) Subjective quality of life and satisfaction with medication which will be assessed at the beginning and end of the intervention period using the 11 item scale established in the DIALOG trial [22]. The scale contains 11 items asking patients to rate their satisfaction with 8 life domains and 3 treatment aspects, one of which is medication, on a scale ranging from 1 (lowest satisfaction) to 7 (highest satisfaction).

f) Continuation with financial incentives (in intervention group only) and adherence during a 6 month follow up period will be taken from the medical records.

g) Teams in the intervention group will be asked after 6 months, 12 months and 18 months about all aspects of experiences with the scheme including whether patients on the scheme asked for an increase of the incentive, and whether other patients with hitherto good adherence also asked for financial incentives and/or became poorly adherent in order to be eligible for the incentives. This will be done using open questions with a written documentation of the answers.

Simple measures of subjective quality of life and satisfaction with medication are the only patient reported outcome criteria used in the study. They have been included to obtain a subjective outcome that reflects the user perspective. However, this will be an element that patients can participate in or not. If they do not consent to be contacted for completing the scale at the end of the intervention period, they will still participate in the trial, and there are no mandatory patient rated or interview based criteria. The patients to be recruited for the trial have been 'difficult to engage' in care, and many may refuse participating because they do not want to be interviewed by a researcher or complete questionnaires. This would result in difficulties to recruit and - more importantly - a significant selection bias.

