## Methods

### Design

In a cluster randomised controlled trial, community teams caring for patients with psychotic disorders in the community, currently AOTs, will be randomly allocated to the intervention group or control condition. The allocation of teams, and not individual patients, will prevent contamination of practice within teams and facilitate the assessment of overall experiences in teams with the practice. It will also make it possible for teams in the experimental group to offer financial incentives to further patients outside the study, without compromising the study design. Teams might consider this to avoid a sense of unfairness among patients cared for by the same team or simply to have more patients benefiting from the intervention. Outcomes will be analysed on the level of individual patients. The effect of clustering of patients within teams will be controlled for in a mixed effects model. The trial will not be 'blind', as masking of patients and clinicians is impossible. Yet, the primary outcome criterion (percentage of injections taken) and secondary outcomes, with the exceptions of global clinical improvement which is rated by clinicians and subjective quality of life and treatment satisfaction which is rated by patients, can be obtained objectively and are taken from the medical records, and should therefore not be influenced by lack of masking.

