### Economic analysis

A cost-effectiveness analysis will be conducted from an NHS perspective, using data on health service use, national unit cost figures and the main outcomes in turn (adherence, time 'slippage' of taking depots, CGI). Incremental cost-effectiveness ratios and cost-effectiveness acceptability curves will be estimated and employed as necessary, generated from the net benefit approach and using bootstrap regression for a range of values of willingness to pay for incremental outcome changes. Sensitivity analyses will examine the impact of altering key assumptions and parameter values. It is usual in any trial to find differences in service access, treatment adherence, baseline characteristics, changes in outcome dimensions over time, cost and cost-effectiveness. In the present study, these variations would be of particular interest, and we therefore plan to analyse patterns within the samples in order to examine whether there are identifiable patterns of inequity with respect to need, socioeconomic group, and key demographic characteristics. The concentration index approach, now quite widely used in health economics for example, offers a robust and informative methodology [24].

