## Discussion

The trial aims to establish the effectiveness and cost effectiveness of offering financial incentives to improve adherence to antipsychotic maintenance medication. The target group are patients with psychotic disorders who do not adhere to medication, although they are likely to benefit from it. The primary outcome is adherence to medication. We assume that an improved adherence to medication will be associated with significant health and social gains for the patients concerned. However, the aim of this trial is only to test an intervention to improve adherence and not whether antipsychotic maintenance medication is indeed effective or not. We therefore decided to use health and social outcomes only as secondary criteria, although improving them is the ultimate objective of the whole intervention.

It would also have been desirable to have patient reported measures, e.g. on their attitude to treatment in general and to medication in particular, as a central outcome. However, the target group of this study are very difficult to engage in care and often even more difficult to engage in research trials. Requiring patients to attend interviews or fill in questionnaires may have limited recruitment and lead to substantial drop out rates. Thus, the ideal research design cannot be implemented because patients are likely not to comply.

We plan to conduct the study with and in AOTs. Yet, given the possible organisational changes in the NHS which can be difficult to anticipate, we may have to deal with teams that are re-configured during the duration of the trial. The research team will try and implement the study protocol despite such changes. We will aim to ensure that the allocation of patients to teams in the experimental arm or control group throughout the study period is not compromised. This may be a challenge since the research team has no managerial or clinical control over the participating clinical teams. We will also aim to assess the general experiences of teams with the practice, e.g. whether other hitherto adherent patients also asked for financial incentives and whether teams continue with offering financial incentives to the study patients after the end of the trial. These general experiences may be highly relevant for a potential wider implementation of the intervention.

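### CGI improvement is rated once, at month 12, by an unmasked consultant; no pre-allocation CGI rating is stated, so change is judged retrospectively and entry severity cannot be adjusted for

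*Protocol article*

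**What the plan says.** All references are to the protocol article.

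- **Outcome measures**, first of the two items labelled b): the construct and instrument are "Clinical improvement as assessed on the Clinical Global Impression Scale (CGI"), rated "by the treating consultant psychiatrist at the end of the 12 month period". The text does not say whether the severity or the improvement item of the CGI is meant. No CGI rating at entry is stated anywhere in the article.
- **Outcome measures**, item e): subjective quality of life and satisfaction with medication, by contrast, are "assessed at the beginning and end of the intervention period using the 11 item scale".
- **Design**: "The trial will not be 'blind', as masking of patients and clinicians is impossible". Among the outcomes that the section excepts from objective collection from records is "global clinical improvement which is rated by clinicians".
- **Economic analysis**: cost-effectiveness is to be estimated for "the main outcomes in turn (adherence, time 'slippage' of taking depots, CGI"), so the CGI is one of three effect measures.
- **Discussion**, on possible changes in the NHS: "we may have to deal with teams that are re-configured during the duration of the trial".

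**The concern.** Improvement is a change, and a change needs a starting point. The article leaves two readings open, and both have a gap.

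If the consultant gives a global improvement rating at month 12, it has to be made against the patient's state a year before, reconstructed from recall or from whatever notes exist, by a rater who knows which arm the team is in. Expectation can then colour the remembered starting state as well as the end state. If the team has been re-configured meanwhile, the rater may not have known the patient at entry.

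If the consultant gives a severity rating at month 12, a single cross-sectional score is not improvement, and there is no entry severity on the same scale to adjust for.

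The outcome carries some weight. It is named first among the secondary outcomes in the Abstract, it is the only global clinical rating, and it enters the cost-effectiveness analysis. A later analysis plan could not repair the gap, because no analysis can create a pre-allocation rating that was not collected.

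**Working it through.** No sample size or power figure is stated for the CGI, so there is nothing to reproduce. The check is a reading of the text followed by an illustration of scale.

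**Timing and feasibility, from the text**

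1. Item e) gives a beginning and an end assessment; the CGI item gives an end only. The authors stated a baseline where they planned one.
2. In Design, consultants consent with their team before patients are identified, and patients are recruited before teams are allocated. A window for a rating untouched by allocation therefore exists.
3. Under Inclusion criteria, patients must have been with the team for at least 4 months, so the team already knows them at entry.

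**Scale of chance imbalance**

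Inputs from Proposed sample size: at least 52 patients per arm analysed, and an inflation factor of 1.1 (ICC 0.05, 3 patients per team). That factor was set for adherence; using it for the CGI is an assumption. The CGI is treated as approximately continuous, in SD units.

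- Effective number per arm: 52 / 1.1 = 47.3.
- SE of a chance difference between arms in entry severity: √(2 / 47.3) = 0.21 SD.
- 95% range: ±1.96 × 0.2057 = ±0.40 SD.

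**What a baseline covariate would give for a severity endpoint**

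The correlation r between entry and month-12 severity is not in the article; 0.4 to 0.6 is assumed. Residual variance is multiplied by 1 − r². The difference detectable with 80% power (two-sided 5%) without adjustment is (1.960 + 0.842) × 0.2057 = 0.58 SD; adjustment multiplies it by √(1 − r²). An entry imbalance of 0.40 SD passes r × 0.40 into the unadjusted month-12 score.

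| Assumed r | Cut in residual variance | Detectable difference, 80% power | Carry-over of a 0.40 SD imbalance |
|---|---|---|---|
| 0.4 | 16% | 0.53 SD | 0.16 SD |
| 0.5 | 25% | 0.50 SD | 0.20 SD |
| 0.6 | 36% | 0.46 SD | 0.24 SD |

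**What a baseline covariate would not give**

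Suppose that unmasked raters at month 12 favour one arm by b SD when there is no true effect. The two-sided 5% error becomes 1 − Φ(1.96 − b/0.2057) + Φ(−1.96 − b/0.2057). For assumed b of 0.1, 0.2 and 0.3 SD this is about 8%, 16% and 31%. The article gives no basis for choosing b, and a rating at entry does not change it.

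**The case against.** The strongest reply has five parts.

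- **Silence in a condensed article is not proof of absence.** The full protocol is not shown and could contain a baseline CGI. Item e) involves the patient, so its timing had more reason to be spelled out. This stands as a limit on the wording: none is stated, which is less than saying that none exists. The contrast within one list still makes mere brevity the less likely explanation.
- **Randomisation already deals with entry severity.** A reader might infer that the arms cannot be compared without a baseline rating. The article does not support that. Teams are randomised after patient recruitment, the comparison is balanced on severity in expectation, and the standard error of an unadjusted comparison allows for chance imbalance. What is lost is adjustment and precision.
- **The rating need not rest on memory.** A reader might infer that it does, but nothing stops the consultant using case notes. Nothing requires it either, so the supportable word is retrospective.
- **Re-configuration of teams is only a possibility.** The Discussion says that it may happen and does not mention consultants changing. If raters did change, the two proposed ratings could come from different people. That would probably weaken the correlation, but the entry rating would still be a valid covariate.
- **The lack of masking is disclosed.** Design names this outcome as an exception to objective collection. That is correct, and the new point is the missing entry rating. It would also be wrong to say that an entry rating removes half, or any stated share, of rater bias: no such fraction can be derived, and the month-12 rating stays unmasked.

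**Conclusion.** The point holds as a limitation of one secondary outcome. The article states a single, unmasked, month-12 rating of improvement and no pre-allocation CGI. Improvement is therefore judged retrospectively by a rater who knows the allocation, and a chance imbalance in entry severity (95% range about ±0.40 SD, if the adherence inflation factor also applies to the CGI) could not be adjusted for on that scale. The comparison between arms remains balanced on entry severity in expectation.

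The 16% to 36% cut in residual variance depends on the assumed correlation of 0.4 to 0.6 and applies only to a month-12 severity endpoint. It does not measure the weakness of a retrospective improvement rating, which cannot be sized from the article. The primary outcome, taken from records, is unaffected, and so are the other two effect measures in the economic analysis. The change is worth making because it is cheap and can only be made before allocation.

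**What to change.** Name the CGI item to be used. Have the treating consultant rate CGI severity for each recruited patient after patient consent and before the team is allocated, and again at month 12. Analyse month-12 severity adjusted for the pre-allocation rating, within the mixed model already planned for clustering, and use that estimate in the CGI cost-effectiveness ratio. Keep the global improvement item as supportive. Report that the month-12 rating remains unmasked.

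The cost is one short extra clinician rating per patient, 34 × 4 = 136 in all, by consultants who have already consented. It needs no patient contact, so the article's reason for keeping patient assessments to a minimum is not affected. The downside is a little consultant time.

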### Planned interventions

Patients in the AOTs that have been allocated to the intervention will be offered a financial incentive for each depot injection of anti-psychotic medication for a 12 month period. Patients will receive £15 for one injection with the total sum not exceeding £60 for a four-week period (the maximum number of injections is 4 per month). The administering clinician will give the money in cash directly after the injection. Patients will sign a receipt. There are several reasons to set a standard sum of £15 for each depot injection:

• A fixed sum per injection simplifies the practice and makes it transparent for all clinicians and patients involved.

• The sum of £15 is in line with the successful open pilot study in East London.

• The sum is below the limit of £20 per week which would interfere with patients' disability benefits. Most patients eligible for the study receive Disability Living Allowance, Income Support with Disability Premium, or Incapacity Benefit. In all of these cases, patients are not entitled to have a separate income of more than £20 (including therapeutic earnings and income through research participation) without having their benefits reduced.

• £15 per injection is intended to be an incentive helping persuade otherwise ambivalent patients. Yet, it is important to limit the total sum to a maximum of £60 per four weeks so that patients do not become financially dependent on the additional income. The money is intended to provide an incentive, but not lead to financial dependence on the scheme.

Otherwise all patients will receive treatment as usual. The type, frequency and dosage medication and all other interventions will not be affected by participation in the study.

Members of the research team will attend meetings of each AOT in the intervention group and discuss again the practice of offering financial incentives and the nature of the study. Following that there will be a brief training programme on the exact procedure. The procedure of the intervention will also be outlined in a written manual. All teams will then be regularly visited by the research assistants and, if required, also by members of the team of applicants. A discussion of the practice at a team meeting will be repeated after 6 months of the intervention period.

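### The incentive is costed as a per-team staff estimate, although the trial's own records give it exactly for each trial patient

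*Protocol article*

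**What the plan says.** All references are to the Protocol article.

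- **Outcome measures, item c (costs of care).** Use of health services "will be obtained from case notes and electronic administrative data bases". The intervention has its own rule: "Costs for the intervention will be estimated for each participating team from information provided by staff".
- **Planned interventions.** "Patients will receive £15 for one injection with the total sum not exceeding £60 for a four-week period". Cash is handed over straight after the injection, and "Patients will sign a receipt".
- **Outcome measures, primary outcome.** "Adherence will be measured, objectively, as the percentage of prescribed depot injections actually taken". A count of injections taken is therefore needed for every patient.
- **Design.** Allocating whole teams will "make it possible for teams in the experimental group to offer financial incentives to further patients outside the study". Outcomes are analysed per patient.
- **Economic analysis.** Acceptability curves are to be "generated from the net benefit approach and using bootstrap regression", with adherence, slippage and CGI as the effects in turn.

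The article does not say whether receipts will be used for costing, whether non-trial payments will be left out, or how a team figure becomes a patient's cost.

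**The concern.** The rule fixes a unit (the team), a method (an estimate) and a source (staff) for the intervention's cost. For the incentive component, the trial already holds something better on all three counts: a patient-level count at a known price, backed by a signed receipt.

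Two things could go wrong under the literal rule.

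1. A team figure need not equal the cost of the trial patients, because intervention teams may also pay others. Any such error falls in the intervention arm only and passes straight into the incremental cost.
2. A net-benefit regression pairs each patient's cost with that patient's effect. Incentive cost rises with injections taken, so it is tied to adherence. A team average blurs that tie within teams.

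**Working it through.** **Inputs.** £15 per injection and a £60 four-week cap (Planned interventions); 4 recruited patients per team and 5 to 8 eligible in most teams (Design); SD of adherence 31 percentage points, ICC 0.05 and 85% adherence in the experimental arm (Proposed sample size). *Assumptions:* injection intervals of one, two or four weeks (the article gives no mix) and willingness to pay of £10, £20 or £50 per percentage point of adherence.

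**1. The plan's own figure.** 4 × £15 = £60 per four weeks, which agrees with the stated cap. Over 13 such periods the maximum is 13 × £60 = £780.

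**2. Incentive cost per patient-year, costed directly** (£15 × injections paid):

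| Assumed interval | Full adherence | At 85% | SD (31%) |
|---|---|---|---|
| Weekly | 52 × 15 = £780 | £663 | £242 |
| Two-weekly | 26 × 15 = £390 | £331.50 | £121 |
| Four-weekly | 13 × 15 = £195 | £165.75 | £60 |

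**3. If non-trial payments entered the team total.** With m further patients paid equally and the total divided by the 4 trial patients, the ratio to the true cost is (4 + m)/4:

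- m = 1 (5 eligible): 1.25
- m = 2: 1.50
- m = 4 (8 eligible): 2.00

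The overstatement is 25% to 100% of the incentive cost. With m = 0 the arm mean is exact.

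**4. If a team average were assigned to each patient.** Within one injection interval, incentive cost is kE, where E is percentage adherence and k is £7.80, £3.90 or £1.95 per point (weekly, two-weekly, four-weekly). Its correlation with E is 1; across mixed intervals it is lower. The mean of a team of 4 has correlation with a member's own adherence of √[(1 + 3 × 0.05)/4] = √0.2875 = 0.54. About 71% of the variance (1 − 0.2875) is averaged out.

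**5. Spread of patient net benefit, incentive cost alone.** With own cost, SD = |λ − k| × 31. With the team average, SD = √(λ²v + k²b − 2λkb), where v = 31² = 961 and b = 0.2875 × 961 = 276.3. Ratio of the second to the first:

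| Assumed interval | λ = £10 | λ = £20 | λ = £50 |
|---|---|---|---|
| Weekly | 3.87 | 1.48 | 1.13 |
| Two-weekly | 1.48 | 1.18 | 1.06 |
| Four-weekly | 1.18 | 1.08 | 1.03 |

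The 3.87 arises because λ (£10) is close to k (£7.80), so the SD with own cost is small (£68).

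**6. What averaging leaves alone.** Replacing each patient's cost by the average over the same team members does not change the team's mean cost, and so not its mean net benefit. The distortion in step 5 is therefore within teams. It would reach an interval built by resampling individual patients. An unadjusted comparison that resamples whole teams would not show it. The article does not state the resampling unit.

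**The case against.** The strongest reply is that the sentence is being read too narrowly.

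- The cost of the intervention is wider than the £15. It includes team meetings, training and clinicians' handling time, for which a team estimate from staff is the natural method. **This stands**, and the fix keeps it.
- Staff make the payments, so what they report may well include the receipts. **This stands as a possibility**; the article neither says so nor rules it out.
- Nothing says that a team average is assigned to patients. A cost derived for each team could be applied to each patient's own injection count. **This stands**: the loss in steps 4 and 5 is conditional.
- Apportionment is detail that a fuller economic plan may settle. **This stands in part.** A missing detail would be no finding, but the article does state a rule, and for the incentive component a better one is available from data the trial collects anyway.

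A reader might infer two stronger conclusions, and the document supports neither. The first is that incentive cost will be biased upwards. The article says only that teams might pay others; it does not plan to count those payments or to divide them over trial patients. The second is that averaging destroys the cost-effect covariance and so invalidates the interval and the acceptability curve. Averaging weakens the patient-level part for one cost component and leaves the between-team part. Inpatient, outpatient and other service costs come from records, and their covariance with effect is untouched.

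**Conclusion.** The point holds as a low-cost improvement, not as a demonstrated error. The stated rule estimates at team level a component that is known exactly per trial patient, and as worded it does not separate payments to patients outside the trial.

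The possible overstatement of 25% to 100% applies to incentive cost alone. It rests on three assumptions: all eligible patients are paid equally, their payments are counted, and the total is divided over the 4 trial patients. The drop in correlation from 1 to about 0.54 rests on team averaging, teams of 4, the planning ICC of 0.05 and a single injection interval. The effect on the cost-effectiveness conclusion cannot be sized. The incentive is at most £780 per patient-year, and the article gives no total cost of care to set against it. The effect may be small.

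**What to change.** Replace the single sentence under costs of care with a two-part rule:

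1. **Incentive component.** Cost it per trial patient as £15 times that patient's receipted injections, checked against the depot record. Use the receipts as the primary count, since a patient may leave the scheme and still take injections. Exclude payments to patients outside the trial. Enter this patient-level cost in the net-benefit regression.
2. **Set-up, training and handling time.** Keep the team-level staff estimate, apportioned over all patients whom the team pays, so that trial patients do not carry the whole team's overhead.

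The cost is one changed sentence and the copying of counts from receipts that the procedure already produces. Patients are asked for nothing further.
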